### Study design

The PERCEIVE study will use a randomized controlled experimental design. A total of 216 women with traumatic birth experience will be recruited within 14 days postpartum and randomized to either the early EMDR intervention or CAU. Women will be asked to participate by their midwife or by the researchers at the end of the postpartum midwifery care period, which is 8 to 10 days postpartum. To ensure sufficient time to read the patient information and provide written consent, randomization has been set to take place at 14 days postpartum. Patients in the early EMDR therapy group will receive two sessions of EMDR therapy between 14 and 35 days postpartum as it is expected that a time frame of 3 weeks (21 days) is feasible to ensure adherence of participants to the protocol. Patients in the CAU group will receive no EMDR treatment but will receive two telephone calls during the study period. The two groups will be compared on a number of outcome variables before (T0 = 2 weeks) and post-treatment (T1 = 9 weeks; see Figs. 1 and 2). The study endpoint (T1) is at 9 weeks postpartum to establish the possible presence of PTSD accurately as defined by the DSM-5 criteria for PTSD.

**Fig. 1 Fig1:**
[figure not shown]
Flow chart

**Fig. 2 Fig2:**
[figure not shown]
Enrolment and assessments over time

Women will be recruited in a large hospital and several community midwifery practices in the Amsterdam area, the Netherlands. We expect that the study duration will encompass 2 years from start inclusions to end inclusions. The study protocol is approved by The Medical Research Ethics Committee of the OLVG Hospital and registered with trialregister.nl (reference no. NL73231.000.20).

### Patients

#### Inclusion criteria

Women less than 14 days postpartum who report a traumatic birth experience will be asked to participate in this study. Medical deliveries as well as women who had a delivery supervised by a primary care midwife from community midwifery practices in Amsterdam will be included. Furthermore, they must understand the Dutch language.

#### Exclusion criteria

Exclusion criteria include age less than 18 years old, birth trauma related to a previous birth, recent diagnosis of a psychiatric disorder, recent or current worsening of symptoms of a previously diagnosed psychiatric disorder requiring treatment or a recent history of a suicide attempt, that is, less than 3 months prior to the beginning of the study.

### Procedures and interventions

When women agree to participate, they will receive a home visit from the researchers to ensure women acknowledged the information and to fill out an informed consent. After screening and providing informed consent, participants will be randomly allocated to either the EMDR therapy or the CAU group within 14 days postpartum (see Fig. 1). Randomization will be on a 1:1 basis by block randomization with random block sized of two, four or six, performed using Castor EDC [38]. After completing the baseline assessments (T0), participants will be informed in which group they have been randomized.

#### The EMDR therapy group

Participants in the EMDR therapy group will receive two treatment sessions between 14 and 35 days postpartum, consisting of 60 min each [39]. The EMDR therapy sessions will be conducted in an out-hospital clinic by trained psychologists who have completed both the basic and advanced EMDR therapy training course accredited by the Dutch National EMDR Association (www.emdr.nl) and have at least 1 year of experience with providing EMDR therapy. When the participant or therapist is not able to be physically present because of the COVID-19 epidemic, therapy sessions may, by exception, be conducted digitally. Digital psychological interventions during COVID-19 are supported by the American Psychiatric Association and the British Psychological Society [40, 41].

The essence of EMDR therapy is that the therapist aims to reduce the vividness and emotionality of trauma memories by asking the patient to recall the trauma memory while simultaneously making eye movements [42, 43]. The EMDR therapy will be implemented with the use of rapid deployment of sets of eye movements offered by fingers or using a light bar [39]. In case of any adverse events during the study period, the EMDR therapist will report this to the researcher and set up an individual plan with regard to the wishes and needs of the participant.

#### The CAU group

The CAU group will receive care as provided currently which means no treatment for their traumatic birth experience. However, participants in this group will receive two telephone calls between 14 and 35 days postpartum to monitor the course of symptoms regarding their traumatic birth experience. These conversations will be conducted by the researcher. Preferably, no professional psychological treatment will be given during the study period as to not bias the results. Therefore, when a participant is stable but wishes to receive EMDR treatment, she will be asked to wait for therapy until she has filled in the last questionnaires and the Clinician-Administered PTSD Scale of DSM-5 (CAPS-5) interview is conducted at the end of the study period (T1). When symptoms of PTSD significantly worsen during the study period, women will be referred to their general practitioner who can then refer the patient to a psychologist or psychiatrist when needed. When professional psychological help regarding the birth trauma is started within the study period, this will be registered and reported as a deviation of the protocol.

### Assessments

#### Screening

After giving birth, all maternity women will receive a flyer with information about the study, regardless of the type of delivery or the presence of birth complications. Eight to 10 days postpartum, all women will be asked the following question: ‘How did you experience the delivery of your baby?’ Depending on the place of the delivery, this question will be asked either by the researcher or by their own midwife. Women will be considered eligible for the study if the answer includes the word ‘trauma’ or ‘traumatic’, or when the patient indicates to suffer from symptoms appropriate to PTSD.

#### Safety

Safety of early intervention EMDR will be monitored by the therapist. The occurrence of all adverse events, which is defined as increased suicidal ideation, serious self-injurious behaviour or contacts with healthcare providers in case of mental health crisis, will be reported to the researcher. Safety of participants in the CAU group will be monitored by the researchers. Based on regular phone calls, it will be estimated whether additional interventions regarding their psychological symptoms are indicated. For both groups, the researcher will register the adverse event and the general practitioner will be informed to take appropriate measures to ensure the safety of the participants.

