### Interrater reliability and treatment fidelity

Patients, therapists and researchers will not be blinded due to the nature of the study. Assessment of the CAPS-5 interview will be conducted by an independent trained clinical interviewer, who is not aware of the randomization result. The therapists are independent of the research team and work at different sites outside the hospital. Patients in the EMDR therapy group will be randomly and equally distributed among therapists. All EMDR sessions will be recorded on video and randomly rated for treatment fidelity. During the entire study, duration group supervision every 2 to 3 months is obligatory for all therapists. After each first session with a new patient, a case conceptualization will be sent for supervision including the story of the traumatic event, with a hierarchy of the most relevant traumatic moments (targets) regarding the current impairment. Deviations from the protocol will be noted and reported. If known, therapists register when a patient terminates the study and the reason for stopping. Furthermore, they inform the PI about it as soon as possible. Women who withdraw from treatment will be invited to fill in the previously mentioned questionnaires and the CAPS interview.

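### The between-arm adverse-event comparison may be confounded by ascertainment that differs by arm and is unblinded; asking all women the same questions at T0 and T1 would largely cure this

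*Protocol article*

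**What the plan says.** The Aim section makes safety part of the main objective, defines it as freedom from a short list of events (worsening suicidal thoughts, serious self-injury, crisis contacts) and hypothesises that early EMDR is safe.

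The Safety section assigns monitoring by arm. For EMDR: "Safety of early intervention EMDR will be monitored by the therapist". For CAU: "Safety of participants in the CAU group will be monitored by the researchers", and then "Based on regular phone calls, it will be estimated whether additional interventions regarding their psychological symptoms are indicated".

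The contacts that carry this monitoring are set out under the two arms. For EMDR: "Participants in the EMDR therapy group will receive two treatment sessions between 14 and 35 days postpartum, consisting of 60 min each". For CAU: "participants in this group will receive two telephone calls between 14 and 35 days postpartum to monitor the course of symptoms". If an adverse event occurs in the EMDR arm, "the EMDR therapist will report this to the researcher and set up an individual plan". The Safety section adds a step common to both arms: the researcher registers the event and the general practitioner is told.

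Under Interrater reliability and treatment fidelity, therapists and researchers are stated to be unblinded; only the CAPS-5 interviewer is unaware of allocation. The same section says: "Women who withdraw from treatment will be invited to fill in the previously mentioned questionnaires and the CAPS interview".

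The Effectiveness section describes T1, at 9 weeks, as a CAPS-5 interview plus the T0 questionnaires, the same in both arms. The article gives T1 no role in collecting adverse events. Statistical analysis, Primary study parameters, plans chi-square tests of adverse-event prevalence between arms.

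**The concern.** A between-arm test of event counts is a fair test of risk only if an event has the same chance of being found in each arm. Here the finder, the mode of contact and its purpose all depend on allocation. In one arm the person delivering the treatment looks for harm during hour-long therapy sessions. In the other a researcher looks for it by telephone, in calls of unstated length meant to follow symptoms. Both know the allocation.

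The bias could run either way. Longer contact may bring more events to light under EMDR. A therapist judging the effects of her own treatment, or a woman who stops attending, may bring fewer.

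What is at stake is the safety half of the main aim. The Background says that safety data on early intervention after recent trauma are limited, and Data management explains that no data monitoring committee is planned. The chi-square comparison is the only between-arm safety analysis the article describes. Unequal ascertainment cannot be repaired in the analysis afterwards.

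**Working it through.** **1. The two arms side by side**

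| Feature | EMDR | CAU | Same? |
|---|---|---|---|
| Who looks for events | treating therapist | researcher | no |
| Route | two 60-minute therapy sessions | two telephone calls, length not stated | no |
| Blinded | no | no | yes |
| Number of contacts | 2 | 2 | yes |
| Window | day 14 to 35 | day 14 to 35 | yes |
| Registration and notice to general practitioner | by the researcher's procedure | same | yes |
| T1 interview and questionnaires | yes | yes | yes, but no adverse-event role described |

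The matched rows concern the amount of contact and what happens once an event is known. The two unmatched rows determine whether it becomes known.

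**2. The plan's own figures**

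The article states no adverse-event rate, detection probability or power for safety, so there is no safety figure to reproduce. Its sample size does reproduce. With a difference of 10 and an SD of 20, a two-sided t-test at 0.05 with 86 per arm has power 0.903, and 86 / (1 − 0.20) = 107.5, rounded up to 108. This is used below only as the arm size.

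**3. How unequal detection would act (illustration on assumed values)**

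Let p be the true risk and s the probability that an event is found. The observed risk is p × s, so the observed risk ratio is (p1 × s1) / (p2 × s2). With equal true risk it reduces to s1 / s2.

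Example at an assumed 5% true risk in both arms: 108 × 0.05 × 0.9 = 4.86 events found against 108 × 0.05 × 0.7 = 3.78, a ratio of 1.29.

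Probability that an uncorrected chi-square test at 0.05 rejects, by exact binomial enumeration, 108 per arm, equal true risk:

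| Detection (assumed) | Observed ratio | risk 2% | 5% | 10% | 20% |
|---|---|---|---|---|---|
| 0.9 vs 0.9 | 1.00 | 0.039 | 0.044 | 0.053 | 0.050 |
| 0.9 vs 0.7 | 1.29 | 0.039 | 0.057 | 0.087 | 0.127 |
| 0.9 vs 0.5 | 1.80 | 0.049 | 0.108 | 0.212 | 0.403 |
| 0.9 vs 0.3 | 3.00 | 0.070 | 0.228 | 0.466 | 0.802 |

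Swapping the arms inverts the ratios and leaves the rejection rates unchanged.

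A real difference can also be hidden. Take true risks of 10% and 5% with detection 0.5 and 0.9: the observed risks are 0.10 × 0.5 = 0.050 and 0.05 × 0.9 = 0.045, a ratio of 1.11, and the test rejects with probability 0.047. With detection 0.9 in both arms the ratio is 2.0 and the probability is 0.263.

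**4. Reading**

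Unequal detection can create or mask a difference. With a modest detection gap or rare events the effect on the test is small. Which row applies cannot be learned from the article.

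**The case against.** The best defence is that the article matches more than it leaves unmatched. Both arms have two scheduled contacts in the same three-week window. Registration and notice to the general practitioner are common. T1 is a scheduled contact, identical in both arms, with a blinded interviewer. A condensed article may also leave adverse-event forms to the full protocol. All of this is correct, and it rules out several stronger readings that a reader might infer.

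- *That the test compares detection instead of risk.* The documents do not show this. They support only that the two may be confounded.
- *That a woman who stops EMDR loses her only safety channel.* Therapists, where they know it, record the reason for stopping and inform the principal investigator, and she is still invited to the questionnaires and interview. The route is imperfect, but it exists.
- *That events are handled quite differently, so that the same crisis counts in one arm only.* The therapist must report the event as well as make a plan, so the plan does not remove it from the count. Referral of a worsening CAU woman to her general practitioner is not by definition a crisis contact. Some differential counting is possible; the text does not establish it.
- *That nobody looks for harm after day 35.* Day 35 to day 63 (9 × 7) is 28 of the 49 days from T0 to T1, but this counts days between contacts, not missed events. The provisions for adverse events and for worsening symptoms refer to the whole study period, and a question at T1 could cover the interval.
- *That the missing baseline for suicidal ideation is an error.* Which item defines an increase is a form-level detail that an article may omit.

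What the defence does not meet is the rule the article does state: who monitors, and by what route, depends on the arm. Common registration begins only after an event has been found.

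**Conclusion.** The point holds in limited form. As written, the adverse-event comparison may be confounded by arm-specific, unblinded ascertainment, because the treating therapist monitors one arm and the researcher monitors the other by telephone. This follows from a stated design rule, not from a detail left out.

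The size and direction of any bias cannot be derived from the documents. The ratios and rejection rates in the working rest on assumed risks, assumed detection probabilities, 108 women contributing per arm and an uncorrected chi-square test. They show what unequal detection can do, and none of them, including the ratio of 1.80, is an estimate for this trial. The change is a worthwhile, cheap improvement; the weakness does not invalidate the trial.

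**What to change.** Add one short set of identical fixed questions on the listed events (suicidal ideation, self-injury, crisis contact) to the T0 and T1 questionnaires, for all women in both arms, including those who stopped EMDR. The T1 questions should cover the whole period since randomisation. State in Statistical analysis that the between-arm comparison uses these answers. Report all therapist-registered and phone-registered events by arm alongside, as descriptive data, so that no known event disappears from the report. Amend the Safety section to match. Existing monitoring and care stay as they are.

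Costs and limits:

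- The work is a few items, a small amendment and two wording changes.
- The comparison then depends on T1 completion. The sample size allows for up to 20% loss (108 × 0.8 = 86.4, about 86 per arm), and loss may itself be related to harm.
- Recruitment began in September 2020, so women already enrolled may lack the T0 items, the T1 items or both. Their number should be reported by arm.
- Women know their allocation by T1, so identical questions equalise the route but not that knowledge.
- Answers on suicidality must be read promptly under the existing safety procedure, which adds some workload.

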#### Effectiveness

Other outcome variables will be assessed using multiple questionnaires. After randomization, but prior to the treatment (T0), both groups will receive the PTSD checklist for DSM-5 (PCL-5) [44], World Health Organization Quality of Life Questionnaire-BREF (WHOQOL-BREF) [45], Postpartum Bonding Questionnaire (PBQ) [46], Wijma Delivery Expectancy/Experience Questionnaire version B (W-DEQ B) [47], Early Postpartum Depression Scale (EPDS) [48] and questions on breastfeeding (see Figs. 1 and 2). While the experiences of the women are leading in this study, the results of patients’ questionnaire scores will not influence the inclusion and randomization process. Questionnaires will be sent through Castor with a unique ID code. If participants do not have access to a computer, the questionnaires will be provided on paper with a return envelope.

Nine weeks postpartum (at T1), each participant in both groups will undergo a CAPS-5 interview [49] and will receive the same questionnaires as at T0. To establish whether the time criterion (i.e. criterion F) of the DSM-5 criteria for PTSD has been met, the CAPS-5 interview will be conducted 4 weeks after the last EMDR therapy session in the intervention group, which corresponds to 9 weeks postpartum. The CAPS interview will be conducted by an independent person who is blinded to the randomization and who has received official training in assessment of the CAPS as to not bias the results. The CAPS version regarding symptoms in the last month will be used.

### Instruments

The following measurement instruments will be used:

#### Posttraumatic Stress Disorder Checklist (PCL-5)

The PCL-5 is a 20-item self-report questionnaire corresponding to the symptoms in the DSM-5 and is rated from 0 (not at all) to 4 (extremely) [44]. Total symptom severity scores ranging from 0 to 80 can be obtained by summing the scores for each of the 20 items. A total score ≥31 has been found suggestive for a probable PTSD in the English version [50]. Additionally, symptom clusters following the different DSM-5 criteria can be analysed separately [51]. A previous study found strong internal consistency, test-retest reliability, convergent validity and discriminant validity of the PCL-5 [52]. The reported clinically significant change on a DSM–IV version of PCL was found to be 10 points [53]. For the PCL-5, this clinically significant change has not been set yet.

#### Clinician-Administered PTSD Scale for DSM-5 (CAPS-5)

PTSD diagnosis as well as PTSD symptom severity will be assessed by using the Dutch version of the CAPS-5 [49, 54]. The CAPS-5 is a structured clinical interview that enables standardized DSM-5 PTSD diagnosis based on symptom severity scores. The interview consists of 20 questions regarding PTSD symptom severity (B–E items) and several questions concerning other DSM-5 criteria. PTSD diagnosis can be made by following the DSM-5 diagnostic rule, which requires the A criterion (exposure to (imminent) dead, severe injury or sexual violence), ≥1 B item (questions 1–5), ≥1 C item (questions 6–7), ≥2 D items (questions 8–14), ≥2 E items (questions 15–20), the F criterion (duration ≥1 month), G criterion (causing significant suffering or disability) and H criterion (symptoms are not caused by another medical condition or substance use). Questions regarding the B-E criteria are rated from 0 (‘absent’) to 4 (‘disabling’). Symptoms rated ≥2 are included in the calculation for the diagnosis. To assess whether criterion A was met during birth, specific questions will be used according to the work of Alcorn et al. [55]. The exact questions are as follows: (1) ‘Did you feel that your life or your baby’s life was threatened during or after birth?’ (2) ‘Did you think that you or your baby might die?’ (3) ‘Did you experience an actual injury or threat of serious injury around the time of birth?’ (4) ‘Did your baby experience an actual injury or threat of serious injury around the time or birth?’ [55]. High validity and reliability of the CAPS-5 have been found [49, 56].

#### World Health Organization Quality of Life assessment (WHOQOL-BREF) [45]

Quality of life is measured by using the Dutch version of the WHOQOL-BREF. It contains 26 items covering four domains: physical health, psychological health, social relationships and environment. Domain scores can be transformed to a score ranging from 0 to 100 with higher scores reflecting better quality of life. There is no cut-off point to demonstrate better or worse quality of life in this particular population. It has been validated for this specific population [57].

#### Postpartum Bonding Questionnaire (PBQ)

Mother to infant bonding is assessed by using the PBQ [46]. It consists of 25 statements, each followed by a 6-point Likert scale ranging from ‘Always’ (0) to ‘Never’ (5) with a range of 0–125 with higher scores reflecting a problematic mother-to-infant bond. Good validity and reliability of the Dutch version of the PBQ have been found [58]. To analyse the effects of PTSD symptom severity on the PBQ, only the total score will be used since later validation studies have not been able to replicate its factor structure. A score of 26 or higher is suggesting for some kind of bonding disorder, whereas a score of 40 or higher indicates severe bonding disorders [59].

#### Wijma Delivery Experience Questionnaire version B (W-DEQ B)

The W-DEQ B is used to measure postpartum fear of childbirth. The W-DEQ is a 33-item self-report questionnaire assessing FoC during pregnancy (version A), and after delivery (version B) in terms of the woman’s cognitive appraisal of childbirth [47]. It was designed as a monofactorial scale, all 33 items being scored on a 6-point scale leading to a sum score between 0 and 165, with a higher score equalling more FoC. High reliability and promising validity of the W-DEQ B have been found [47].

#### Edinburgh Postnatal Depression Scale (EPDS)

The Dutch version of the EPDS is a self-reporting questionnaire designed to assess pregnancy and postpartum depression; it is composed of 10 items scored on a 4-point Likert scale. Higher scores reflect a greater level of depression severity with a cut-off score of ≥13 to screen positive for depression [60]. The Dutch version of EPDS is a widely used measure with good psychometric characteristics [48].

